#### Daytime functioning

We will objectively measure physical activity using the Actiwatch-2® described earlier. The accelerometer at the wrist reflects whole body activity. Successful use of wrist actigraphy to quantify physical activity was reported in recent studies involving subjects with chronic illness [59, 60]. We subjectively measure daytime functioning using the PROMIS Physical Function Scale CAT version described above.

#### Treatment exposure (dose)

We examine adherence to COPD-ED and AC by keeping attendance records and CBT-I by attendance and examining sleep diary and actigraphy data. As part of each CBT-I session, sleep data are reviewed, and problems with adhering to the plan are discussed. Phone calls for assistance or to answer questions are documented.

#### Power analysis

Power analysis for aim 1 is based on main effect differences at the end of the intervention. We estimated the per cell sample size assuming a moderate effect size (Cohen’s *d* = 0.5), alpha = 0.05, and power = 0.80 using the fpower SAS macro available at http://www.datavis.ca/sasmac/fpower.html. Based on combined data from our pilot study measures, the minimum detectable difference (MDD) for the treatment main effects will be clinically meaningful. For example, we will be able to detect a 2.3-point difference in insomnia severity between those receiving COPD-ED versus those not, averaged across the other treatment conditions. The MDD for other outcomes includes Actiwatch® sleep efficiency = 6.72, CRQ-F = 0.51, and the Profile of Moods States Fatigue subscale (POMS-F) = 2.76. Between-group effect size estimates from our pilot study ranged from 0.35 for sleep efficiency to 1.03 for insomnia severity, comparing the proposed treatment components. Path models using 7–14 parameters can be estimated according to the sample size convention of 10 to 20 cases per parameter [61], thus, our simple path models can be estimated. We further conservatively estimate an attrition rate of 15 % by the end of the study. Therefore, we will enroll a total of 166 and retain 140 (35 per group) subjects in the proposed study.

#### Recruitment

The majority of subjects will be recruited through the University of Illinois at Chicago Medical Center (UICMC) and the Hines Veterans Administration (VA) Medical Centers; campus, newspaper and radio advertisements, social networking and community outreach. We contact local pulmonologists to recruit subjects through their medical practices. We also use online recruitment strategies such as Research Match. There is a focused recruitment for minorities by placing advertisements in newspapers that serve predominantly the minority communities. Similar techniques are used for women, placing advertisements in publications predominantly read by women. We employ a number of retention strategies that were successfully implemented in our pilot study.

Subjects are initially contacted by mail or advertisement, which will provide a brief description of the study. Potential subjects are asked to return a “Permission to Contact” form with their phone number so the researcher can contact them about the study. The researcher explains the study and answers questions over the phone. If the caller is interested in pursuing the study further, a preliminary health screening is conducted over the phone to determine their potential eligibility for participation. An information brochure is mailed to the home when callers want time to think before making a decision. They contact us again if they decide to pursue being in the study.

## Methods: assignment of interventions

A randomization schedule was developed using Excel whereby the four treatment groups were randomly ordered in blocks of four and sequentially assigned through REDCap according to stratum. We have four strata defined by sex and COPD severity (two levels); this process is managed separately by site. The complexity of the design (four treatment arms × four strata × two sites) is assumed to reduce predictability for the sequence of group assignment for any given participant. Non-blinded study staff generate allocation by REDCap and assign participants to interventions. Personnel administering and scoring the PFTs, actigraphy and posttest/follow-up sleep diaries are blinded to group assignment.

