Excluding the screening, participants have a total of eight or nine laboratory visits (six intervention, pretest, posttest and follow-up). The 3-month follow-up is completed at home or in the laboratory. After the 1-week at-home monitoring period, they are scheduled for the baseline (pretest) visit at either the UIC CON Center for Narcolepsy, Sleep and Health Research (CNSHR) or the Hines VA. Upon completion of the baseline testing, subjects are randomly assigned to group. Subjects recruited from the Hines VA attend the six intervention visits there. Subjects recruited from outside of the VA attend the six intervention visits at the UIC CNSHR. For the 3-month follow-up, subjects either come to UIC or Hines VA for a final visit or they are mailed a packet containing an actigraph, questionnaires and a self-addressed, stamped return envelope. We track attendance using attendance records and the sleep diary. All tests are performed in the same order for each subject. Tests and questionnaires are administered in a private, comfortable room. We make every attempt to minimize selection and performance bias, attrition and missing data. Selection bias is minimized by use of the randomized controlled trial design. Staff performing data analysis are blinded to group assignment. We use strategies to reduce attrition such as good communication between research staff and participants, minimizing participant burden by the use of PROMIS CAT instruments, and monetary incentives. When subjects do not complete the study, we document the reasons data are missing in order to evaluate the missing data using justified assumptions.

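### A single block size of four for four arms lets anyone who tracks a site-by-stratum list deduce the last assignment of each completed block, and the design's complexity does not prevent this

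*Protocol article*

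**What the plan says.** The protocol article, under *Methods: assignment of interventions*, says that "the four treatment groups were randomly ordered in blocks of four and sequentially assigned through REDCap according to stratum". There are four strata (sex by two levels of COPD severity), and "this process is managed separately by site", which gives 4 × 2 = 8 lists. No other block size is mentioned.

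On prediction, the section says only that the complexity of four arms by four strata by two sites "is assumed to reduce predictability for the sequence of group assignment for any given participant".

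On roles: "Non-blinded study staff generate allocation by REDCap and assign participants to interventions". Blinding is claimed for other people: "Personnel administering and scoring the PFTs, actigraphy and posttest/follow-up sleep diaries are blinded to group assignment". *Data collection* adds the data analysts. That section also fixes the timing: "Upon completion of the baseline testing, subjects are randomly assigned to group". Under *Power analysis*, 166 participants are to be enrolled and 140 retained. *Trial status* says recruitment is ongoing.

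**The concern.** A block of four for four arms contains each arm exactly once. After three assignments in a block the fourth is fixed, and after two only two arms remain. Dividing the trial into eight lists would hide this only if the observer could not tell which list the next participant belongs to. Here that is known: lung function is measured at the first screening visit, sex is evident, and site follows from where the participant was recruited. Staff who are not blinded and who make the assignments have the information needed to follow each list.

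If foreknowledge reached anyone with discretion over entry, it could influence who is encouraged, whether a borderline judgement on clinical stability or other health problems goes one way or the other, or the order in which baseline visits are scheduled. That would be selection bias, and it could affect objective and self-reported outcomes alike. *Data collection* relies on the randomized design to minimize selection bias, and that protection depends on assignments being unpredictable.

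**Working it through.** **Inputs.** Four arms, block size four, four strata and two sites (*Methods: assignment of interventions*); 166 assignments (*Power analysis*). The article gives no figure for predictability, so there is none to reproduce. The enrolment figure agrees with its own basis to within rounding: 140 / 0.85 = 164.7, against 166 stated.

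**1. Best guess by position in a block, for someone who knows the earlier allocations on that list.**

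| Place in block | Arms still possible | Chance of a correct guess |
|---|---|---|
| 1 | 4 | 1/4 |
| 2 | 3 | 1/3 |
| 3 | 2 | 1/2 |
| 4 | 1 | 1 |

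Mean over a complete block: (1/4 + 1/3 + 1/2 + 1) / 4 = (25/12) / 4 = 52.1%. Chance alone gives 25%. The number of strata or sites does not enter this calculation.

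**2. How many assignments are fully determined.** This is the number of completed blocks, the sum of floor(n/4) over the eight lists. The leftovers on each list are 0 to 3. Because 166 leaves a remainder of 2 on division by 4, the leftovers must total 2, 6, 10, … up to 22.
- Most: (166 − 2) / 4 = 41.
- Fewest: (166 − 22) / 4 = 36.
- With an average leftover of 1.5 per list: (166 − 8 × 1.5) / 4 = 38.5.

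So 36 to 41 of 166 (22–25%) are certain. Simulation of 166 participants gave a mean of 38.5 with eight equally likely lists and 38.6 with markedly unequal ones.

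**3. Correct guesses over the whole trial, allowing for unfinished blocks.** An unfinished block with 0, 1, 2 or 3 filled places contributes 0, 1/4, 7/12 or 13/12 expected correct guesses, a mean of (0 + 0.250 + 0.583 + 1.083) / 4 = 0.479. The total is 38.5 × 25/12 + 8 × 0.479 = 80.2 + 3.8 = 84.0, and 84.0 / 166 = 50.6%. Simulation also gave 50.6%, with equal and with unequal lists.

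**4. What complexity does achieve.** An observer who sees only the pooled sequence and guesses the arm least used so far in the trial was right 35.0% of the time with equal lists and 35.6% with unequal lists. The split into lists therefore lowers predictability from about 51% to about 35%, but only for someone who does not separate the sequence by list.

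**5. Varied block sizes.** The sizes are assumptions, chosen for illustration. The guesser picks the arm least used so far on the list. The first column uses lists of 24; the second uses 166 participants spread over eight lists.

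| Block sizes | Lists of 24 | 166 over eight lists |
|---|---|---|
| 4 only | 52.2% | 50.7% |
| 4 and 8 | 48.0% | 46.8% |
| 8 and 12 | 43.7% | 42.7% |

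With varied and undisclosed sizes, no place in the list is always certain.

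**The case against.** The strongest reply is that the route to bias is not documented. The article does not say that the staff who assign also recruit, screen or judge eligibility, nor that REDCap shows upcoming entries. A condensed article may leave separation of roles to the full protocol. Participants also pass telephone screening, lung function tests, a depression scale, a sleep study and a week of actigraphy before randomization, and assignment already follows baseline testing. All of this stands, and it rules out the inference that selection bias has occurred. It does not remove the risk. Hiding future entries does not stop deduction from past ones, and the next arm on a list can be worked out before a participant completes baseline.

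Four other stronger readings are tempting, and the article does not support them:
- *Every fourth participant enrolled is predictable.* Certainty applies only to the last place of a completed block on one of eight lists, and only for someone tracking that list.
- *The complexity sentence is plainly false.* It is worded as an assumption, and against an observer of the pooled sequence it is right. It fails for staff who know the list.
- *The main outcomes are all self-reported.* Insomnia is also measured by actigraphy, with blinded scoring.
- *The analysis can do nothing about such bias.* The planned covariate adjustment would deal with imbalance on measured factors; only the unmeasured part would remain.

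It is also fair to say that the gain is moderate, since varied blocks do not bring guessing down to 25%, and that the exact sizes are a matter of choice.

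**Conclusion.** The point holds as a statement about predictability. With one block size equal to the number of arms, an observer who tracks a list can deduce 36 to 41 of 166 assignments and guess about 51–52% correctly overall, against 25% by chance. The complexity of the design gives no protection against that observer, although it is the only safeguard against prediction that the section offers.

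This rests on three assumptions: the block size does not vary (none other is stated), earlier allocations on a list are known to the observer, and enrolment reaches 166. That foreknowledge was used, or reached anyone controlling entry, is not shown and should not be inferred. The sample size is unaffected. Because recruitment is still open and the remedy is small, this is a cheap improvement.

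**What to change.** For the remaining allocations, load new lists for each site and stratum with randomly varied block sizes in multiples of four, and withhold the sizes from all staff who recruit or assign. Sizes 4 and 8 bring correct guesses to about 47–48%; sizes 8 and 12 to about 43–44%. Remove the sentence on complexity, or qualify it to say that it applies only to someone who does not follow allocations by list. Keep assignment after baseline testing as already stated.

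The cost is an upload to REDCap and slightly larger possible imbalance within small strata. A block of four holds each arm once, so two arms on a list can differ by at most 1 within an open block; with blocks of 8 or 12 the gap can reach 2 or 3. A list averages about 21 participants in total (166 / 8 = 20.75), and fewer remain to be allocated, so sizes 4 and 8 are the milder choice if enrolment is well advanced. Adjusting the analysis for sex, severity and site deals with the looser balance. *Statistical analysis* already names severity and gender as example covariates, so site is the one to add.

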## Methods: data collection, data management and analysis

### Data collection

Screening procedures include an initial telephone screening to determine eligibility. Potential subjects are then scheduled for their first screening visit, which takes place at the CNSHR. At that visit, after informed consent is obtained, PFTs are performed, followed by questionnaires. Reliability and validity of pulmonary function testing have been previously demonstrated [62, 63]. The Hospital Anxiety and Depression Scale (HADS) [64] is administered to screen for major depressive symptoms. The HADS was designed for outpatients with medical illnesses, and it has been widely used in people with COPD [65–67]. Reliability and validity were demonstrated [68]. A cutoff score of 11 on the HADS depression subscale is used for depression [64]. A clinical questionnaire is completed at this visit to characterize the sample in terms of demographics and health history. Blood specimens are sent to Quest Diagnostics® for measurement of C-reactive protein and ferritin level. These tests are done in order to rule out anemia and to adequately describe the sample and may be used as covariates in the analyses.

The screening includes a one-night sleep study at home or at the UIC Sleep Science Center or the Hines VA Sleep Laboratory. The sleep study is used to screen potential subjects for sleep apnea, and low SaO_2_ during the night. Objective evidence of any primary sleep disorder according to standard clinical criteria is used to exclude subjects. The remaining subjects receive instructions for continued actigraphy monitoring by wearing an actigraph on their non-dominant wrist at home for a total of 1 week. They are instructed on how to complete the daily sleep diary.

Excluding the screening, participants have a total of eight or nine laboratory visits (six intervention, pretest, posttest and follow-up). The 3-month follow-up is completed at home or in the laboratory. After the 1-week at-home monitoring period, they are scheduled for the baseline (pretest) visit at either the UIC CON Center for Narcolepsy, Sleep and Health Research (CNSHR) or the Hines VA. Upon completion of the baseline testing, subjects are randomly assigned to group. Subjects recruited from the Hines VA attend the six intervention visits there. Subjects recruited from outside of the VA attend the six intervention visits at the UIC CNSHR. For the 3-month follow-up, subjects either come to UIC or Hines VA for a final visit or they are mailed a packet containing an actigraph, questionnaires and a self-addressed, stamped return envelope. We track attendance using attendance records and the sleep diary. All tests are performed in the same order for each subject. Tests and questionnaires are administered in a private, comfortable room. We make every attempt to minimize selection and performance bias, attrition and missing data. Selection bias is minimized by use of the randomized controlled trial design. Staff performing data analysis are blinded to group assignment. We use strategies to reduce attrition such as good communication between research staff and participants, minimizing participant burden by the use of PROMIS CAT instruments, and monetary incentives. When subjects do not complete the study, we document the reasons data are missing in order to evaluate the missing data using justified assumptions.

#### Enactment and fidelity

The clinician interventionalists are trained in CBT-I, COPD-ED, CBT-I + COPD-ED, and the AC education topics by experts. They observe several sessions being conducted by a clinician experienced in the interventions and practice the interventions under supervision. They use a manual developed during the pilot research to guide the sessions. In order to assure high-quality sessions, samples are reviewed and scored for adherence to the protocol. Subject adherence is also tracked. Adherence to stimulus control and sleep restriction is assessed at each session using the sleep diary and/or actigraph. Evaluation of adherence to stimulus control is assessed by examining responses to a sleep diary question that asks how the participant managed periods awake during the night. Evaluation of adherence to sleep restriction is assessed by comparing the recommended time in bed to the reported time in bed.

### Data management

Data are entered onto a REDCap application and stored on a secure server with daily back-ups. The raw data are stored in locked file cabinets that are housed in our research laboratory protected with a security lock. Only the immediate research staff (PI, key personnel) have access to these data files. The computerized data files are password-protected and available only to the immediate research staff (PI, key personnel). Identifiable elements are needed during the study, for instance in order to contact subjects for data collection appointments. Data are coded so that subject identifiers are on data sheets. All data are checked for completeness and validity. The quality of the data is monitored at least annually by the principal investigator (PI) assisted by the research specialists.

### Statistical analysis

#### Test of specific hypotheses

Descriptive statistics (means, standard deviation, frequency) and plots are used to screen the data prior to our main analyses. Necessary transformation and imputations are conducted based on the raw data distribution. Baseline adjustment for covariates (e.g., age, COPD severity (PFT), and gender) will be incorporated into the main effect analyses to reduce error variance and improve statistical power [69]. Data analyses is performed using SAS 9.3 statistical software (SAS Inc., Cary, NC, USA) and Mplus 6.0 (Muthén & Muthén, Los Angeles, CA, USA). All tests will be two-sided and an error rate of *α* <0.05 will be considered statistically significant. The test of each specific aim is described below, and all statistical analysis will employ an intent-to-treat approach. A fully specified statistical analysis plan will be written before unmasking.

Aim 1: to determine the efficacy of individual treatment components, CBT-I and COPD-ED, on insomnia and fatigue. In this 2 × 2 design, participants are randomized into four groups created by crossing the two factors, CBT-I versus AC1 and COPD-ED versus AC2 (see Table 3). We hypothesize that both components will improve insomnia and decrease fatigue following the six-session program, and that participants will maintain these gains at 3 months post intervention. Our factorial design permits the test of an interaction between the two treatment components, and we will assess for the presence of a strong interaction effect. However, we do not anticipate a strong synergy of the treatments since our pilot work showed that both had within-group improvement, and the hypothesized mechanisms for change differ. If the interaction is negligible, we will proceed with the interpretation of averaged main effects as shown in Table 3. The statistical tests for both components will be more robust than tests against a simple control condition because they are averaged across the levels of the other treatment. That is, the effect of each component will be tested controlling for the effect of the other. This is an efficient design because all subjects will be used to test both components. Finally, it may be more acceptable to participants since all receive supportive contact and only one out of four conditions does not receive a component hypothesized as an active treatment for insomnia in COPD patients. We will employ mixed-effects models using insomnia and fatigue as time-varying dependent variables and treatment groups as fixed effects. Demographic and clinical characteristics will be entered as time-invariant covariates if baseline group differences are observed despite randomization. Individuals’ baseline sleep measures and change over time (i.e., intercept and slope) will be modeled as random effects. The null hypothesis will be rejected if a significant treatment × time interaction is observed. For example, a significant CBT-I × time effect in the hypothesized direction would mean that participants receiving CBT-I improved more than those who did not, averaged across the other conditions. The mixed models will be run using PROC MIXED SAS 9.3 (SAS Inc., Cary, NC, USA) and estimated by residual maximum likelihood (REML). Covariance pattern structures (compound symmetry and unstructured) will also be examined, and models will be compared using likelihood ratio tests or Akaike’s Information Criteria (AIC) which is a function of the log likelihood and can be compared across models.

**Table 3 Tab3:** Study design

Study design	CBT-I	AC1	Main effect COPD-ED
COPD-ED	35	35	70
AC2	35	35	70
Main effect CBT-I	70	70	

*AC1* attention control 1, *AC2* attention control 2, *CBT-I* cognitive behavioral therapy for insomnia, *COPD-ED* COPD education

Aim 2: to define the mechanistic contributors to the outcomes after CBT-I and COPD-ED. We hypothesize that CBT-I and COPD-ED components impact insomnia and fatigue through complementary mechanisms. We have previously shown that CBT-I was related to beliefs about sleep, sleep habits, self-efficacy for sleep, and that COPD-ED was related to management of COPD and emotional arousal, thus making them both appropriate candidates for an insomnia treatment approach for COPD patients. We will employ path analysis to test the conceptual model illustrated in Fig. 1 [70]. The model will test whether each treatment component is related to change in the hypothesized mediator, and whether that change is associated with improvement in the outcome. Direct and indirect treatment effects will be estimated. We will conduct path analyses as follows: (1) specification, (2) identification, (3) estimation, (4) testing of fit, and (5) respecification [71]. Potential moderators suggested by our previous work include gender, initial insomnia and fatigue severity, and inflammation and will be tested as interactions of the effect of each treatment component on the outcomes. Variables found to be a significant moderator of treatment will be tested further to determine if the effect is due to a moderated impact on significant mediator variables. Path models assume that variables used to describe relationships are manifest variables and measured without error. While we recognize that it would be preferable to estimate a measurement model, the feasible sample size for this study precludes more complex modeling. Thus, we acknowledge this limitation and will restrict path analysis to reliably measured variables, that is, with internal consistency of 0.80 or higher. Mplus (version 6) will be used to estimate the path models. The root-mean-square error of approximation (RMSEA) and Bentler’s Comparative Fit Index (CFI) will be reviewed to assess model fit. An adequate fit of the data to the model is indicated by a RMSEA value less than 0.08 and a CFI greater than 0.90.

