### Outcomes (dependent variables)

#### Insomnia

We objectively assess insomnia using the Actiwatch-2® (MiniMitter, Philips Respironics, Carlsbad, CA, USA) actigraph. Scoring of actigraph data with standardized computer algorithms is reliable and valid relative to polysomnography [42, 43]. Editing is done with sleep diary information because actigraphy tends to overestimate sleep during quiet nocturnal wakefulness, but is useful in measuring treatment effects [44]. The accelerometer is worn on the non-dominant wrist for a minimum of 4 days at each data collection. Insomnia variables measured include sleep onset latency (SL, minutes to fall asleep after lights out), wake after sleep onset (WASO, minutes spent wake after sleep onset), number of awakenings after sleep onset (NA), total sleep time (TST) and sleep efficiency (SE, time spent asleep divided by time in bed).

We subjectively measure insomnia severity using the Sleep Impairment Index (SII) [29, 45] and a sleep diary. The SII includes seven items, each rated on a 5-point scale (0 = not at all, 4 = extremely) to evaluate: sleep onset severity, sleep maintenance, early morning awakening problems, satisfaction with current sleep, interference with daily functioning, impairment attributed to the sleep problem, and level of distress caused by the sleep problem. Total scores range from 0 to 28, with high scores indicating greater insomnia severity. Validity and reliability were demonstrated in older people with insomnia [45]. A 6-point reduction is recommended to represent a clinically meaningful improvement in individuals with insomnia [46]. The sleep diary is completed by all CBT-I participants in the morning at breakfast time for a 1-week baseline period. Subjects receiving CBT-I complete sleep diaries daily during the six-session intervention period, for 1 week at the end of the intervention; and for 1 week at the 3-month follow-up. The sleep diary is completed by participants not receiving CBT-I for 1 week at baseline; 1 week at the end of the intervention; and 1 week at the 3-month follow-up. Sleep variables as above including SL, WASO, TST, EMA and SE are derived from the diary. Variables are calculated for each night and a weekly mean is computed. Sleep diaries have demonstrated validity and reliability in measuring insomnia in terms of sleep latency and waking after sleep onset [47, 48].

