#### Fatigue

We measure the frequency and intensity of fatigue experienced in the previous 2 weeks using the Chronic Respiratory disease Questionnaire – Fatigue (CRQ-F) [49]. This consists of four items, scored on a 7-point Likert scale. Lower scores indicated more fatigue. The minimal clinically significant change in the CRQ score is associated with a change of 0.5, and a moderate change is associated with a change of 1.0 [50]. In our pilot study, people with COPD reported a mean improvement of 0.75 in mean score of the CRQ-F Scale after CBT-I, suggesting a clinically meaningful improvement in symptoms. Validity and reliability of the CRQ-F was demonstrated in people with COPD [49, 51, 52]. The Cronbach’s alpha for the CRQ-F in our pilot study of people with COPD and insomnia was 0.91. We measure the general feeling of fatigue using the PROMIS Fatigue CAT version described above.

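### No primary outcome is named among about 13 insomnia and fatigue outcomes all tested at 0.05, and the power section cites an unmeasured fatigue scale and an unsupported claim of clinical meaning for the SII

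*Protocol article*

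**What the plan says.** All references are to the protocol article.

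- **Error rate** (Test of specific hypotheses): "All tests will be two-sided and an error rate of *α* <0.05 will be considered statistically significant". The same section promises a full analysis plan before unmasking; that plan is not shown.
- **Decision rule** (Aim 1 analysis): insomnia and fatigue are the dependent variables of mixed models, and the null is rejected on a significant treatment × time interaction. The text does not say on which variable. It reads a significant effect as benefit when it lies in the hypothesised direction.
- **Outcomes** (Insomnia; Fatigue): five actigraphy variables (SL, WASO, NA, TST, SE), five diary variables (SL, WASO, TST, EMA, SE), the SII, the CRQ-F and PROMIS Fatigue. None is called primary.
- **Power** (Power analysis): the calculation is for main effects at the end of the intervention, "assuming a moderate effect size (Cohen’s *d* = 0.5" with "alpha = 0.05, and power = 0.80". Four detectable differences follow and are described together as clinically meaningful. The example is that "we will be able to detect a 2.3-point difference in insomnia severity"; the last is "and the Profile of Moods States Fatigue subscale (POMS-F) = 2.76".
- **Fatigue as measured** (Fatigue): besides the CRQ-F, "We measure the general feeling of fatigue using the PROMIS Fatigue CAT version described above".
- **SII benchmark** (Insomnia): "A 6-point reduction is recommended to represent a clinically meaningful improvement in individuals with insomnia".

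**The concern.** The article goes beyond leaving multiplicity open. It sets a flat error rate for all tests and a rejection rule that points to no single outcome, over a list of variables of equal standing. Read as written, a significant result on any one of them, for either component, could be reported as efficacy on insomnia or fatigue. The reader of the final report would not know how many chances the trial had.

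The power section should have shown which outcome the trial is built around, but it does not. It gives four detectable differences without ranking them. One belongs to a scale that appears nowhere else in the article, while a fatigue scale that is measured has none. The statement of clinical meaning is also illustrated with an SII figure for which the article offers no supporting benchmark. A just-significant SII result could then be presented as clinically important on the strength of that sentence alone.

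**Working it through.** **Inputs.** Two-sided 0.05 for all tests; d = 0.5; power 0.80; 35 per cell, so 70 per level of each factor (Table 3); 15% attrition; 166 enrolled and 140 retained; detectable difference of 2.3 points for insomnia severity and 0.51 for CRQ-F; benchmarks of 6 points (SII) and 0.5 (CRQ). The correlations among outcomes below are assumptions; the article gives none.

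**1. The plan's own sample size.** A two-sample t-test at d = 0.5, two-sided 0.05 and 80% power needs 63.8, so 64 per level, or 32 per cell. The plan has 35 per cell. With 70 against 70, power at d = 0.5 is about 84% (0.836 by t or F, 0.841 by the normal approximation). The effect detectable at 80% power is about 0.48 SD (0.477 by t; normal approximation (1.960 + 0.842) × √(2/70) = 0.474). Enrolment: 140/0.85 = 164.7, against 166 stated. The size is adequate for one outcome per component.

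**2. Number of tests.** 5 actigraphy + 5 diary + 1 SII + 2 fatigue = 13 outcomes; 13 × 2 components = 26. This count is built from the outcome sections, as the article does not list its tests.

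**3. Chance of at least one significant result when neither component has any effect.**

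- Either direction, independent tests: 1 − 0.95^26 = 0.74 (per component 1 − 0.95^13 = 0.49).
- Favourable direction only, 0.025 per test, independent: 1 − 0.975^26 = 0.48 (per component 1 − 0.975^13 = 0.28).
- Correlated outcomes: simulated, with 13 equally correlated normal test statistics per component, all aligned so that improvement is positive. The two components are treated as independent, so both = 1 − (1 − per component)².

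| Assumed correlation | Either direction, both components | Favourable, per component | Favourable, both components |
|---|---|---|---|
| 0 | 0.74 | 0.28 | 0.48 |
| 0.5 | 0.56 | 0.17 | 0.31 |
| 0.7 | 0.42 | 0.12 | 0.23 |

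For comparison, one primary outcome per component gives 0.025 per component in the favourable direction, and 1 − 0.975² = 0.049 over both.

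**4. Fatigue scales.** The measures sections name two fatigue scales, CRQ-F and PROMIS Fatigue. The power section names CRQ-F and POMS-F. POMS-F is absent from the measures sections, Table 2 and the abbreviation list. In SD units the detectable difference for PROMIS Fatigue is the 0.48 SD of step 1; the article gives no SD with which to turn it into points.

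**5. Clinical meaning.** CRQ-F: 0.51 against a benchmark of 0.5, so the wording is supported. Insomnia severity: 2.3 points, with 6 points as the only SII benchmark, and that one defined as a reduction in individuals. The SD implied by 2.3 is 2.3/0.5 = 4.6 to 2.3/0.474 = 4.9. No benchmark is given for sleep efficiency or POMS-F.

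**The case against.** The strongest reply is that this is a condensed article. A full analysis plan is promised before unmasking and a registration is cited; either may name a primary outcome and a multiplicity rule. The 26 tests are also a reconstruction, and the article never says that each sleep variable is a separate claim. This stands as a limit: the finding concerns what the article fixes, namely 0.05 for all tests and a rejection rule not tied to an outcome, and the count is approximate.

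A reader might infer that a false efficacy claim is more likely than not. The documents do not support that. The figures above one half count significant worsening as well, whereas the article reads benefit only from an effect in the hypothesised direction. In that direction the chance stays below one half even under independence. Independence is itself implausible, since the same sleep variables are scored by actigraph and diary.

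A reader might set 2.3 against 6 and call the SII target far too small, or the trial underpowered for a meaningful effect. A difference between group means and a reduction within an individual are different quantities, and a mean difference need not reach a responder threshold. Power for a 6-point mean difference would be above 99.9% at the implied SD. What remains is that the article offers nothing to support the wording for the SII.

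A reader might also note that the pilot effects "ranged from 0.35 for sleep efficiency to 1.03 for insomnia severity, comparing the proposed treatment components" and conclude that sleep efficiency is underpowered at 0.35. Those effects compare the two components with each other, so they estimate neither against attention control. The article discloses the figure and states its assumption of 0.5 openly. That is not an error.

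Finally, the POMS-F line may be left over from the pilot measures. It changes no sample size, but it still describes an outcome that the trial does not have.

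**Conclusion.** The point holds in this form: the article names no primary outcome, applies 0.05 to every test, and leaves about 26 component tests able to support an efficacy statement. With no true effect, the chance of at least one favourable significant result is about 0.23 to 0.48, depending on an assumed correlation between 0.7 and 0, against 0.049 with one primary outcome per component. These figures rest on the reconstructed count of 13, equal correlation among outcomes and independence of the two components.

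Two statements in the power section also need correction: the POMS-F figure, with none for PROMIS Fatigue, and the description of 2.3 insomnia-severity points as clinically meaningful. Neither affects the sample size, which is sufficient for one outcome per component.

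**What to change.** Before unmasking:

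1. Name one primary outcome and time point for each component. The SII at posttest (T2) is one candidate: it fits the lead example in the power section and its end-of-intervention basis, and 70 against 70 gives about 84% power at d = 0.5 with 0.05 per component.
2. Treat the remaining outcomes, including actigraphy, as secondary. Either control multiplicity among them or report them with confidence intervals and no stand-alone efficacy claim.
3. Replace the POMS-F figure with the detectable difference for PROMIS Fatigue, about 0.48 SD at 80% power.
4. Drop the description of the 2.3-point SII difference as clinically meaningful, and report by component the proportion of participants whose SII falls by at least 6 points. This uses the benchmark at the individual level at which the article defines it.

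The cost is wording and no additional patients. The downside is that fewer outcomes can carry a claim. This weighs most on the objective sleep measures, which the central hypothesis places alongside the subjective ones; if the investigators want actigraphy to support a claim of its own, the multiplicity-controlled option in step 2 allows it.
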